#### Management as usual

MAU consists of the standard care offered to adolescents and their families who meet eligibility criteria for the trial in each of the sites. This treatment is likely to be diverse and may involve no therapeutic intervention or individual- or family-oriented work. It is likely to be delivered by a wide range of practitioners with different theoretical orientations. The average duration of these interventions is also likely to vary. It is expected that practitioners will be working in line with best practice as specified in relevant Social Care Institute for Excellence and NICE guidance [2,30].

Based on assessments, the young people in the MAU group receive a tailored range of interventions aimed primarily at preventing reoffending. As in MST, typical interventions are extensive and multicomponent, consistent with the complex mental health needs of this population in the UK [64]. Interventions include helping the young person to re-engage in education; help with substance misuse problems and anger management; social problem-solving skills training; and awareness programs relating to vehicle crime, violent offending and knife crime. It is likely that victim awareness and reparation interventions will be included as appropriate. The treatments are delivered by professional social workers, specialist therapists or probation officers.

The key differences between MST and MAU are that MAU interventions are not normally delivered in a family context by a single person. Typically, no overarching model governs the selection of treatments, and there is no set of principles comparable to that of MST to organise the therapies offered. Rather, interventions are likely to be offered on an ‘as needed’ basis by specialist agencies to which the young person is referred. The young people allocated to MAU are likely to receive considerable attention from a range of professionals delivering evidence-based protocols. In a recent RCT comparing MST with usual services provided by YOT, clients typically received around 21 professional appointments over the period that MST was administered [44,65]. It is unlikely that practitioners in MAU receive the extent or quality of supervision available for MST therapists. However, it is by no means clear that, even during the trial period, MAU interventions are likely to be less intensive or less costly than MST, although they are likely to be delivered in a less focused and less well-specified manner, with greater variability in service provision. In the Brandon Centre trial [44], young people in the control arm attended significantly more appointments than those in the MST arm. This was in line with the National Standards set out by the UK Youth Justice Board for the key contact and enforcement community [66].

For this reason, MAU interventions in the current trial are carefully monitored using a service use schedule designed specifically for the trial, which records contact with all services (health, social, YOT, education, voluntary sector, and so on), including the number of contacts (and possibly the average duration of contacts). This will give a realistic sense of the level of intensity of MAU in whatever form, and, used in conjunction with the MST arm, will give an indication of shifts in intensity - that is, whether the addition of MST reduces the need for other support. As START is a pragmatic trial involving a number of collaborating services even within each individual site, it was not possible to specify in advance what MAU would constitute.

### Assessments and outcome measures

To maximise the clinical validity of the outcome evaluations, assessments are being made across multiple domains using multiple methods and sources.

#### Primary outcome

The primary outcome is the proportion of cases assigned to long-term (3 months or longer) out-of-home placements in specialist residential provision, including placement into local authority care, incarceration, long-term hospitalisation and residential schooling, at 18 months following randomisation. The investigators expect this trial to give information on how many children assigned to MAU and MST require specialist residential provision either immediately or during the follow-up period.

#### Secondary outcomes

The number of secondary outcomes is limited to reduce the measurement burden of the study, which was found to be a disincentive to continued participation in the Brandon Centre study [44]. The domains that the investigators consider key to the intervention are youth offending outcomes, adolescent well-being outcomes and family functioning outcomes. In addition, the economic data collected alongside these outcomes are considered highly important. The study is also designed to collect data on variables that target key mechanisms of change identified in previous MST studies - parent-adolescent relationships and young people’s associations with deviant peers - and to evaluate parenting skills in detail, given that MST aims to improve young people’s lives by targeting caregivers as being primarily responsible for facilitating change. Adolescent symptoms have been shown to decrease in association with increased supportiveness and decreased conflict between parents [67,68] and with an increased caregiver follow-through on discipline practices [69]. Further, adherence to the MST manual by therapists appears to improve family functioning, which in turn decreases deviant peer affiliation, leading in turn to decreased delinquent behaviour [50].

#### Objective measures

Objective secondary outcomes will be collected from reports of offending behaviour based on police computer records, including details of custodial sentences. These measures will be taken at 6-monthly intervals, for the 6 months before randomisation, the 6 months covering the intervention period, and 6-monthly until the 18-month follow-up point. The number of records of offending behaviour (count data) will be obtained and 6-month periods free of any offending behaviour will also be recorded (binary data). Records are obtained from the Police National Computer as well as from the Young Offender Information System database at each site; these records detail information on offences, court appearances, criminal orders, police custody records and arrest rates.

Records of school attendance and exclusions will be retrieved from both the local schools themselves and the National Pupil Database to assess educational outcomes.

#### Self-report

The RA administers pre-testing questionnaires during the initial contact with the young person and family after they have given consent to participate in the trial, prior to group assignment (as described above). Post-testing by the RA is scheduled for 6 months after entry into the study; it is envisaged that this will be a minimum of 2 weeks after the family completes the intervention. Follow-up assessments will be made at 12 and 18 months post-randomisation.

Self-report measures of well-being and adjustment, antisocial behaviour, parenting skills and family functioning as well as parental mental health and adjustment are collected.

*Well*-*being and adjustment*. A general assessment of well-being is taken using the Strengths and Difficulties Questionnaire [70]. Educational outcomes will include evaluation of participants’ emotional and behavioural functioning in the classroom using the Conners Comprehensive Behaviour Rating Scale-Teacher report form [71]. Depression will be monitored using the Short Mood and Feelings self-report questionnaire [72], completed by the youths.

*Antisocial behaviour*. The prevalence and incidence of delinquent behaviour such as vandalism, theft and burglary will be monitored using the Self-Report Delinquency measure [73]. Noncompliance and increasingly serious forms of antisocial behaviour, together with young people’s perceptions of law-abiding behaviour and institutions, will be measured using the Antisocial Beliefs and Attitudes Scale [74]. Peer delinquency will be assessed using the Self-Report Delinquency measure [73]. The investigators predict that MST will achieve decreases in associations with other antisocial peers, increases in positive peer relations and greater commitment to prosocial activities (for example, education). This prediction is consistent with the model and hypothesised mediating mechanisms [50] and is relevant to social policy initiatives and concerns.

*Parenting skills and family functioning*. The quality of the parent-adolescent relationship, family functioning and parenting practices will be evaluated using the Family Adaptability and Cohesion Scales [75] and the Alabama Parenting Questionnaire-Short Form [76]. Parental disruption will be assessed using the short form of the Conflict Tactics Scale [77], and the level of expressed emotion in the home (as conceptualised in the Camberwell Family Interview) will be assessed using the Level of Expressed Emotion questionnaire [78,79].

*Parental mental health and adjustment*. A brief assessment of parental mental health will be obtained using the commonly used screening instrument, the General Health Questionnaire-28 [80].

#### Interviews

*Demographics interview*. A bespoke interview (Demographic Interview for Parents) to cover general family information, including parental forensic history, schooling and economic information, has been constructed and will be administered to all parents. Child psychometrics will be obtained from the Wechsler Abbreviated Scale of Intelligence [81].

*Psychiatric screening*. Psychiatric disorders will be identified and a psychosis screen provided by the Development and Well-Being Assessment [82]. This computerised structured interview measure is administered to both the parents and young person.

*Experience of MST*. Finally, young people and their carer(s) will be interviewed to elicit their views regarding their experience of MST and factors that they perceive had facilitated or inhibited therapeutic change, based on promising qualitative research carried out during the Brandon Centre trial.

#### Health economic evaluation

Health economic analysis will be conducted by the Centre for the Economics of Mental Health at the Institute of Psychiatry, London, to explore the relative costs and cost-effectiveness of MST and MAU. The evaluation will take a broad perspective, including all health, social services, education and voluntary sector services, plus costs to the criminal justice sector, costs resulting from crimes committed, and out-of-pocket expenses to the young people and their families.

Data on MST contacts will be collected directly from the pilot schemes to avoid participants revealing their group allocation to the RAs. Data on the use of all other services will be collected in interviews using the Child and Adolescent Service Use Schedule previously used with young people with complex mental health and social care needs [83-86]. The Child and Adolescent Service Use Schedule will be adapted to the current study population by review of the literature and pilot testing, to ensure comprehensive coverage and face validity. The cost of the trial interventions will be calculated through a detailed micro-costing (or bottom-up) approach using standard costing methodology [87,88], which will involve estimation of the indirect time spent on individual cases, including preparation, meetings, telephone calls and supervision, as well as detailed recording of direct face-to-face contact.

### Moderators of outcomes

#### Therapist adherence to the multisystemic therapy model of intervention

The MST Therapist Adherence Measure-Revised (TAM-R) measures the team’s adherence to the nine MST treatment principles [50]. The TAM-R is a 28-item measure completed by parents or primary caretakers, often administered by the MST team. In the START trial it will be administered independently from the MST team by an RA not associated with that site or the families working with it. Data will be collected from the second week of MST treatment and every 4 weeks thereafter. Research has demonstrated associations between therapist adherence to the MST principles as measured by the TAM-R and youth outcomes [35,39,48,50,89-91].

#### Psychopathic traits and attention deficit hyperactivity disorder

The trial will also evaluate potential moderators that have not been widely explored in previous studies because of sample size constraints, and will consider in particular the role of psychiatric comorbidities including psychopathic traits and ADHD. Young people with high levels of psychopathic traits show a greater likelihood of recidivism [92], and one study found that young children high for CU traits showed poorer outcomes in a parent training programme for children [93]. It is well established that the combination of ADHD and antisocial behaviour is associated with greater amounts of physical aggression, a greater range of persistence of antisocial activity [94] and the persistence of antisocial outcomes in adulthood [95]. Psychopathic traits will be assessed using the Inventory of Callous-Emotional Traits [96], and the Diagnostic and Statistical Manual of Mental Disorders 4th edition ADHD subscales from the Conners Comprehensive Behaviour Rating Scale [71] will be completed by parents and teachers to assess hyperactivity and impulsivity across home and school settings. ADHD diagnoses will also be arrived at categorically using the Development and Well-Being Assessment (see above).

### Programme components of multisystemic therapy and management as usual

A bespoke fidelity measure has been developed to enable accurate characterisation of the programme components of MST and MAU interventions, the Children and Young People – Resources, Evaluation and Systems Schedule (CYPRESS) ([name], [name], [name], [name], personal communication). This approach is based on the initiative of the MST developers [62], who have undertaken a large-scale transportability study with 2,000 families, 429 therapists, 122 supervisors and 20 consultants. Organisational structure and climate as rated by the therapists, supervisors and consultants appears to predict the outcome of MST [97]. CYPRESS was designed to characterise care pathways for antisocial youths in a UK context. It will be administered as an interview to service managers and therapists and will elicit care-pathway-relevant information, for example, in relation to service characteristics, team operations, and the range of interventions available to young people and their families. CYPRESS will allow the identification of key programme elements associated with outcome. More specifically, the use of a common measure will allow comparison between MST and MAU along important dimensions of care and potentially provide information on common aspects of service function associated with outcome. Such an approach has been used to characterise other complex interventions in mental health [98]. It will be of particular value in assessing the key beneficial organisational components of such a complex intervention as MST when it is deployed in a healthcare system radically different from that in which it was developed [99].

### Qualitative interviews

To obtain additional information about the experience of MST and being in an RCT of this treatment, the semi-structured interview developed by Tighe and colleagues in the Brandon Centre trial will be used [100]. This 45-minute interview elicits parents’ and young people’s experience of MST or control treatments, and their views of the costs and the benefits. Semi-structured interviews will be conducted to explore how young people and their parents or caregivers experienced MST, whether they think that the young person’s functioning or carers’ lives have changed following MST (in areas targeted by the intervention), and whether family relationships have changed. If the young person or parent reports changes, the interview will also explore the timing of those changes and how MST affected the changes.

Interviews will be audio recorded and transcribed verbatim. Transcripts will be analysed using framework analysis, a structured method for analysing themes in data, developed by Ritchie and Spencer [101], which facilitates the systematic analysis of large amounts of qualitative data [100]. The researcher develops a structured thematic coding framework for the data, which is then used to systematically record the occurrence of each of the categories in the entire data set. Charts are then developed to show the pattern of occurrences of each theme, and these are used to map and interpret the data set as a whole.

The intention is for the interview to be administered to a random 5% of families across all sites by a person independent of the intervention but not blind to treatment allocation.

### Follow-up assessment

Follow-up assessments will be conducted at 6, 12 and 18 months post-randomisation. Table 2 shows a detailed outline of the planned measures at each follow-up point throughout the trial.

**Table 2 T2:** Assessments and schedule of administration in the START trial of multisystemic therapy

**Assessment**	**Timeline (months)**			
	**Baseline**	**6**	**12**	**18**
**Eligibility and consent**				
Eligibility assessed by MST panel	x			
Consent taken at introductory visit	x			
Randomisation information provided	x			

**Questionnaires****-****Young person**				
Child and Adolescent Service Use Schedule (last two questions)	x	x	x	x
Short Mood and Feelings Questionnaire	x	x	x	x
Inventory of Callous-Unemotional Traits	x	x	x	x
Self-Report Delinquency	x	x	x	x
Level of Expressed Emotion	x	x	x	x
Wechsler Abbreviated Scale of Intelligence	x			
Antisocial Beliefs and Attitudes Scale	x	x	x	x
Strengths and Difficulties Questionnaire	x	x	x	x
Development and Well-Being Assessment	x		x	
Alabama Parenting Questionnaire-Short Form	x	x	x	x
Youth Materialism Scale	x	x	x	x
EQ-5D^a^	x	x	x	x
**Education data**				
Conners Comprehensive Behaviour Rating Scale-Teacher form	x	x	x	x
Attendance/Exclusion rates	x	x	x	x
**Youth offending data**				
Offending history	x	x	x	x
**Interviews**				
Optional Qualitative interview - parent or carer				x
Optional Qualitative interview - young person				x

^a^EQ-5D is a measure of health outcomes (used in the health economic evaluation).

### Statistical analysis plan

All analysis will be according to the intention-to-treat principle. The characteristics of the treatment groups will be described at baseline. Preliminary analysis will investigate the pattern of missing follow-up data.

#### Primary outcome

The primary analysis will be a logistic regression with random effects to account for clustering by therapist. The analysis will include centre, number of past convictions, gender, age at onset of criminal behaviour and other risk indicators as fixed effects. The logistic regression will be fitted using generalised estimating equations. A Wald test of the effect of intervention will be used as the primary analysis. As a secondary analysis, tests of interaction will be used to explore whether the intervention differs according to gender, age, presence of a criminal record or referral path. Clustering by therapist will be accounted for by computing robust standard errors [102].

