### Aims

The primary aim of START is to establish whether MST is more effective than management as usual (MAU) in reducing out-of-home placement in a sample of adolescents at high risk of being removed from their homes because of antisocial behaviour. Secondly, the trial aims to determine whether the provision of MST leads to improved well-being for young people and their families, including improved emotional and behavioural functioning for the young person, closer family relationships, improved parenting skills, improved educational outcomes and reduced offending behaviour. Thirdly, the trial will establish whether MST is cost-effective compared to MAU and results in reduced costs across mental and physical health, criminal justice and educational systems. Finally, in terms of secondary outcomes, the trial will examine the mediators and moderators of treatment change, and determine whether specific groups of young people presenting with antisocial behaviour benefit to a greater or lesser extent from the intervention. Consistent with extant mediational studies of MST trials with a range of juvenile offenders [48,50], we will test whether the MST theory of change is supported in a broader group of antisocial adolescents in the UK; namely, that MST treatment processes will result in improvement on key family and peer risk factors associated with antisocial behaviour, and that improvements in these risk factors will result in decreased adolescent antisocial behaviour.

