In addition, we will improve on previous MST trials, which have rarely examined empirically derived moderators of antisocial behaviour, by studying whether treatment outcome is influenced by the onset of participants’ antisocial behaviour, as well as their level of attention deficit hyperactivity disorder (ADHD) symptomatology and CU traits measured at the beginning of the intervention. Early-onset antisocial behaviour, comorbid diagnoses of ADHD and CD, and high levels of CU traits have been associated with greater severity of antisocial behaviour and poorer youth justice outcomes. For example, early-onset antisocial behaviour has been shown to be the best predictor of early arrest (before the age of 13) and, in turn, young people with an early arrest are the most likely to be chronic offenders by the age of 18 [51,52]. Clinical studies of children with ADHD show that they are at high risk for delinquency [53], and children with comorbid diagnoses of ADHD display more early-onset and severe forms of antisocial behaviour [54]. Research over the past 15 years has demonstrated that antisocial adolescents with high CU traits are more likely to develop severe and violent delinquency over time [55,56], and show more severe and aggressive behaviour [55,57-59]. We propose that young people in the trial showing early-onset antisocial behaviour and high levels of ADHD symptoms or CU traits may benefit less from MST than young people who do not show these characteristics or vulnerabilities.

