#### Secondary outcomes

The antisocial behaviour outcome (time to offence) will be analysed using a Cox regression. All other secondary outcomes will be modelled using linear mixed-effects models, with separate treatment effects for the 6-, 12- and 18-month outcomes and an unstructured covariance matrix. The effect of intervention on the 18-month outcome will be tested using a Wald test. Tests of interaction will be performed for all secondary outcomes in which a nominally significant treatment effect is found.

It is anticipated that the primary outcome will have very little missing data as these data are obtained independently of the participants. For the secondary outcomes, linear mixed models and Cox regression yield valid inferences when data are missing at random (that is, the probability of a particular data point being missing depends only on observed data). It is possible that data may be missing not at random, so sensitivity analyses will be conducted to explore the impact of missing data.

There is just one primary outcome, so the primary analysis will be conducted at a nominal two-sided significance level of 0.05. There are several secondary outcomes, so caveats will be used when interpreting effects of treatment on secondary outcomes. No formal correction for multiple testing will be used.

There is no plan to analyse outcomes by site and it is hoped that TAM-R scores will pick up the variance associated with individual therapists.

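### The stated interaction tests for the primary outcome leave out all three hypothesised moderators, and those for secondary outcomes depend on a significant overall effect

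*Protocol article*

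**What the plan says.** Under Aims, the protocol article says that "the trial will examine the mediators and moderators of treatment change". It then states a hypothesis with a direction: "young people in the trial showing early-onset antisocial behaviour and high levels of ADHD symptoms or CU traits may benefit less from MST". The comparison is with those who lack these features. The section on psychopathic traits and ADHD, under Moderators of outcomes, says: "The trial will also evaluate potential moderators that have not been widely explored in previous studies because of sample size constraints". It adds that the trial "will consider in particular the role of psychiatric comorbidities including psychopathic traits and ADHD", and it names the instruments.

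In the Statistical analysis plan, the Primary outcome paragraph gives the only list of interaction factors in the article, and ranks these tests as secondary: "tests of interaction will be used to explore whether the intervention differs according to gender, age, presence of a criminal record or referral path". Onset appears in that paragraph only as an adjustment variable: "The analysis will include centre, number of past convictions, gender, age at onset of criminal behaviour and other risk indicators as fixed effects".

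The Secondary outcomes paragraph of the same plan names no factors and sets a condition: "Tests of interaction will be performed for all secondary outcomes in which a nominally significant treatment effect is found".

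**The concern.** There are two separate problems.

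1. **The list and the hypothesis do not meet.** A reader who follows the Primary outcome paragraph as written would run four interaction tests and never test the three moderators that the Aims single out. The article is not silent on interactions, which would leave the matter to an analysis plan. It names a list, and that list differs from its own hypothesis.

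2. **The condition on secondary outcomes suits this hypothesis badly.** If some young people benefit less, the average effect shrinks, the main-effect test is less likely to reach significance, and the interaction is then not examined. A main effect that misses significance says little about whether an interaction exists: in a trial with 1:1 allocation the two estimates are close to independent.

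At stake is whether a stated aim has a matching planned test. The primary treatment comparison is not at stake.

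**Working it through.** **The plan's own power figure.** The sample-size section gives 350 per arm, 30% versus 20%, two-sided 5%, power 86%, falling to 83% with a design effect of 1.22 in the MST arm. The two-proportion formula without continuity correction gives 86.5%. With an effective MST group of 350/1.22 = 286.9 it gives 82.6%. Both figures reproduce, and neither depends on the interaction tests.

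**The texts side by side.**

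| Hypothesised moderator (Aims) | In the primary-outcome interaction list? | Where else it appears |
|---|---|---|
| Early onset | No | Minimisation factor (onset of conduct problems); fixed effect (onset of criminal behaviour) |
| ADHD symptoms | No | Moderators section; Conners scales at baseline (Table 2) |
| CU traits | No | Moderators section; CU-traits inventory at baseline (Table 2) |

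The entry for age in the interaction list cannot stand in for onset. The randomisation section treats age (11 to 14, 15 to 17) and age at onset (2 to 11, 11+) as two factors, and the primary model lists age at onset separately.

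**Effect of the condition on a continuous secondary outcome.** The document gives no moderator prevalence, interaction size or retention, so these are assumptions:

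- N = 595 analysed (85% of 700), arms equal, outcome SD 1
- no clustering and no covariate adjustment
- effect d in those without the moderator and 0 in those with it
- moderator prevalence q

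Formulas:

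- Main effect = (1 − q)d, SE = 2/√N = 2/√595 = 0.082.
- Interaction = d, SE = 2/√(N·q(1 − q)). This is 0.164 at q = 0.5 and 0.179 at q = 0.3 or 0.7.
- Covariance of the two estimates = (1 − q)·4/(N(1 − q)) − q·4/(Nq) = 0. The joint probability is therefore the product of the two powers.
- Power = Φ(z − 1.96) + Φ(−z − 1.96).

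| d | q | z main | Main effect significant | z interaction | Interaction power alone | With the condition |
|---|---|---|---|---|---|---|
| 0.3 | 0.3 | 0.21/0.082 = 2.56 | 73% | 0.3/0.179 = 1.68 | 39% | 28% |
| 0.3 | 0.5 | 0.15/0.082 = 1.83 | 45% | 0.3/0.164 = 1.83 | 45% | 20% |
| 0.3 | 0.7 | 0.09/0.082 = 1.10 | 19% | 0.3/0.179 = 1.68 | 39% | 8% |
| 0.4 | 0.5 | 0.20/0.082 = 2.44 | 68% | 0.4/0.164 = 2.44 | 68% | 47% |

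The loss grows with prevalence because more of the sample dilutes the average.

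**Primary outcome, where no condition applies.** Assume 30% placement under MAU in all subgroups, the 1.22 design effect, and a 10-point reduction in those without the moderator against none in those with it. Interaction power is then about 29% at 50% prevalence, 25% at 30% and 20% at 20%. For a 20-point reduction against none it is about 85%, 75% and 62%.

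**The case against.** The strongest reply is that the article condenses a fuller plan. The moderators are stated as an aim, given a direction and tied to instruments, and the measures are scheduled at baseline. The article gives no mediation model either, so its analysis section may cover treatment effects only and leave moderator modelling elsewhere. This stands in part. A missing model would be no finding. A stated list that omits the stated hypotheses, together with a condition that works against them, is one.

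Three stronger readings are tempting and not supported:

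- **That all planned interaction tests omit the moderators.** The omission is explicit only for out-of-home placement. For secondary outcomes, which include the antisocial-behaviour measures closest to the hypothesis, no factors are named at all.
- **That the trial cannot answer its moderator aim, or that any such result would be post hoc.** Nothing forbids the tests, the data are scheduled, and the hypothesis is published with its direction. The Discussion does call its search for subgroups post hoc, but the open questions it cites there are ethnicity, anxiety and depression.
- **That the condition reaches the primary outcome.** It does not; those interaction tests are unconditional.

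Limiting interaction tests when there are many secondary scales and no multiplicity correction is also a recognisable restraint. It is reasonable for exploratory factors and a poor fit for a hypothesised moderator.

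On size, the hypothesis is less benefit, not zero benefit; a smaller but real benefit dilutes the main effect less. Baseline adjustment helps: assuming a correlation of 0.5, d = 0.3 and 50% prevalence, z becomes 1.83/√0.75 = 2.11, and power is 56% alone and 31% with the condition. Without adjustment, interaction power at 0.3 SD stays below 50% even when the condition is removed, so removing it does not by itself give a reliable answer.

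**Conclusion.** The point holds within limits. For the primary outcome, the overlap between the three hypothesised moderators and the four listed interaction factors is nil. For secondary outcomes, the condition (read in its natural sense, as restricting the tests to significant outcomes) tends to suppress the predicted pattern. In the 0.3 SD illustration it removes between about 11 percentage points of interaction power (39% to 28%, at 30% prevalence) and 31 points (39% to 8%, at 70%). At 0.4 SD and 50% prevalence it removes about 21 points (68% to 47%).

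These sizes rest on assumed retention, prevalence and effects, and on no benefit at all in the moderator group; the textual mismatch rests on no assumption. It should be put right, but the primary treatment comparison and the stated sample size and power stand as they are.

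**What to change.** Bring the Statistical analysis plan into line with the Aims and the Moderators section:

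- Name treatment-by-moderator interactions for age at onset of conduct problems, baseline ADHD score and baseline CU-trait score as the pre-specified moderator tests. Keep the last two continuous.
- Apply them to the primary outcome and to the key antisocial-behaviour outcomes.
- Run these tests whatever the main effect.
- Report interaction estimates with confidence intervals and say that power is modest.

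The four factors already listed need no relabelling, since the article presents them as a secondary analysis meant to explore.

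The cost is wording and a few more model fits on data already scheduled. The downside is a few more interaction tests to report with caveats.
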